#### Data Analysis

To evaluate implementation (ie, objective 1), longitudinal mixed modeling accounting for and considering potential methodological issues associated with an interrupted time series analysis (eg, autocorrelation and time-varying confounders) will be used to analyze implementation indicators (ie*,* Assessment of Competencies and Contributors to Enhance Practice Transition to Virtual Family Centered Care survey, therapists’ self-reported FCT frequency, FCT fidelity self-perceived checklist, and PRIME-SP). Changes will be documented in the short term (ie, 1 month after TIPS introduction) and in the long term (ie, at the end of TIPS, 12 months after its introduction). Models will be covariate-adjusted to reduce potential confounding bias, including the therapists’ characteristics (eg, gender and years of experience) and site characteristics (eg, service provided, geography, and general patient characteristics), to estimate associations of key explanatory variables alongside TIPS. Secondary analyses will explore the heterogeneity in changes of outcome measures across genders, sites, therapists, and health jurisdiction levels.

*Secondary implementation objectives* will be evaluated using a multimethod approach.

#### Data Collection and Analysis

The local leadership team, involved in *documenting the coadaptation of TIPS* (ie, objective 2), will be asked to complete a sociodemographic questionnaire to record their characteristics such as years of experience, level of expertise, and previous experience with telehealth services and technologies. An initial draft logic model will be developed by the research team based on the best evidence related to knowledge translation strategies to best address the FCT needs identified by therapists in a national survey and in recent publications. This draft will subsequently be presented to the local site team members for feedback. A *discussion group format* [86] will be used to gather the local leadership team members’ input, which will then be used to coadapt TIPS (ie, logic model, training curriculum, and materials) to site-specific needs. Throughout the coadaptation process, discussions will be audio recorded, meeting documents will be collected, and proposed adaptations and decisions made by local leadership team committee members, and their reasoning for these modifications will be recorded during the discussion group in real-time and in the TIPS logic model, training curriculum, and materials.

To *identify the factors influencing therapists’ intention to adopt and use FCT* (ie, objective 3), *monthly mentoring meeting, audio recordings* and *materials* (eg, meeting agendas and suggested resources), *virtual community of practice discussion thread content*, and *semistructured interview audio recordings* with participating managers, therapist champions, therapists, and families after the implementation of TIPS will be collected. Data will be analyzed thematically using a deductive-inductive approach guided by the Consolidated Framework for Implementation Research domains [77].

### Effectiveness Evaluation

#### Overview

To *evaluate TIPS effectiveness* (objective 4) and *costs* (objective 5), a mixed methods pre-post design has been chosen to measure the intervention effectiveness outcomes and costs using easily accessible service indicators and questionnaires administered to parents. To capture additional effects, semistructured interviews will also be conducted after the implementation of TIPS, with all participant groups. Instruments and processes are described in detail in further sections.

#### Data Collection

At the service level, the *site profile questionnaire*, completed by managers before and after the implementation, includes questions related to organizational readiness for eHealth [87] as well as clinically relevant *wait time indicators* (eg, the average service wait time for service) [88,89]. To estimate changes in wait times (before vs after), a confounder-adjusted analysis using generalized linear mixed effects models will use a log-link function to account for the typically right-skewed nature of time data. Estimated fixed (intervention) effects for the effectiveness outcomes will be reported with Šidák-corrected 95% CIs [76].

To evaluate changes in perceived service quality, the *family questionnaire* will be electronically distributed by managers or therapists to eligible families. It includes a sociodemographic questionnaire (eg, remoteness of location), and *Measurement of Processes of Care-20* (MPOC-20), a valid and reliable 20-item self-reported measure of parents’ perceptions of the extent to which rehabilitation services are family-centered [90]. It contains five scales: (1) enabling and partnership, (2) providing general information, (3) providing specific information about the child, (4) coordinated and comprehensive care for the child and family, and (5) respectful and supportive care; it is scored on a 7-point Likert response scale, which indicates the extent to which the service provider engaged in the behavior (1=not at all to 7=to a very great extent). Each scale yields its own score, and no total score is calculated. Data will be analyzed using generalized linear mixed effects models with nested random effects (families within therapists within sites) to control for the correlated nature of the data (ie, the possibility that families have responded once or twice to the MPOC-20) and to account for therapist and site cluster effects. Analyses will be conducted for each of the 5 MPOC-20 domains and controlled for the same confounding variables described in the analysis for objective 1, as well as for family-level variables (eg, sociocultural background, child’s age, and gender).

To explore all changes in service delivery (both negative and positive), participants will be invited to participate in audio-recorded *semistructured interviews* after the implementation of TIPS. The sample will include all managers, some therapists (all local site champions and a subsample of therapists showing high or low adoption in different sites), and parents with diverse sociocultural characteristics, levels of perception of quality of care, and experience with FCT. Interview data will be analyzed thematically using an inductive approach to better understand the breadth and depth of changes to pediatric rehabilitation service delivery according to various stakeholder perspectives. Integration of quantitative and qualitative data using the aforementioned explanatory approach [91] will allow us to uncover the anticipated and unanticipated effects of FCT on pediatric rehabilitation service delivery.

To *explore costs*, an economic evaluation following a health care perspective as recommended by the Canadian Agency for Drugs and Technologies in Health [92,93] will be used primarily. The research team will maintain a *costs journal* related to TIPS implementation (eg, knowledge brokers’ salary). Costs relating to therapist participation in TIPS (time × average salary) and those resulting from changes in the organizational setting (eg, telehealth equipment) will be documented in the managers’ *site profile questionnaire*. *Families’ costs and savings*, including impact on travel time, parking costs, missed work, and costs related to equipment or internet, will be included in the *family questionnaire*. The total costs related to the implementation of the TIPS will be calculated (ie, additional therapists and knowledge brokers’ time and salary), as well as costs per participating therapist and costs per site accounting for different organizational characteristics. Relative cost, an estimation of costs per session, cost per client seen by the therapist, and incremental ratios (ie, change in costs to use the TIPS divided by change in the primary implementation outcomes measures and secondary effectiveness measures) will also be computed. Finally, societal costs (ie, savings for families in decreased travel time, parking, missed work, and costs related to equipment or internet) will be explored for robustness analysis.

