### Participants

Participants will be recruited from study sites according to the following eligibility criteria:

Managers (n=20; one per site): managers, or their delegates, responsible for rehabilitation services at the site and members of the local leadership team, will participate in the coadaptation of TIPS to their site. Managers may contribute to their site’s monthly mentoring meetings; aid in the recruitment of therapists, parents, a therapist champion, and a parent-partner for their site; and complete site- or service-specific data collection instruments before and after the implementation of TIPS.Therapists (n=600 with 50% anticipated response; n=300): physiotherapists, occupational therapists, or speech-language pathologists providing outpatient pediatric rehabilitation services to children aged 0 to 12 years at each site are recruited via the managers and are interested in using FCT. Therapists will participate in the TIPS program, complete data collection instruments as prescribed, and aid in parent recruitment.Parents (n=20 per therapist with an anticipated response rate of 33%; n=2000 families per assessment time point): 1-time data collection will be undertaken with 2 samples (preimplementation and postimplementation samples) of parents or caregivers who received services (either in-person, virtually, or both) from at least one participating therapist in the previous 3 months.Therapist champion (n=20; one per site): a therapist selected based on their telehealth experience and on peer recognition within their organization. Therapist champions are members of the local leadership team participating in the coadaptation of TIPS to their site and will oversee the monthly mentoring meetings and agree to report on the implementation process after the implementation of TIPS.Parent or patient partner (n=20; one per site): parent or patient partners will primarily be recruited from family, parent, or patient advisory committees at the participating sites or, in the absence of such initiatives, from regional, provincial, or national patient engagement programs. As members of the local leadership team, parent or patient partners will participate in the coadaptation of TIPS to their site and could be called upon to contribute to their site’s monthly mentoring meetings.

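### The stated MPOC-20 model names no site-by-period effect, so if change differs between sites, as the protocol expects, the before-after confidence intervals will be too narrow

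*Protocol article*

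**What the plan says.** Under Effectiveness Evaluation, Data Collection, the protocol article plans for the MPOC-20 "generalized linear mixed effects models with nested random effects (families within therapists within sites"). It gives two purposes for these effects: to allow for "the possibility that families have responded once or twice to the MPOC-20) and to account for therapist and site cluster effects". One analysis is run for each of the five scales, and Šidák-corrected intervals are announced for the effectiveness outcomes.

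The Participants section sets the sampling: "1-time data collection will be undertaken with 2 samples (preimplementation and postimplementation samples"), of parents served "from at least one participating therapist in the previous 3 months". The expected numbers are "n=600 with 50% anticipated response; n=300" for therapists and "n=20 per therapist with an anticipated response rate of 33%; n=2000 families per assessment time point" for parents. There are 20 sites in 6 regions (Sample Size). Table 1 places the MPOC-20 at T-3 and T5, that is, 3 months before and 15 months after the start of implementation.

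Three other statements bear on whether sites change alike. The hypotheses under Research Question and Study Objectives tie better perceived service quality to the sites with the largest change in adoption and fidelity. The Intervention section adapts the webinar to each site. Study Settings trains site by site and staggers rollout by region, 2 months apart.

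**The concern.** A random site intercept describes how good a site is on average. It enters the before mean and the after mean equally and drops out of their difference. The same is largely true of a stable therapist intercept. With only these terms, the model takes it that all sites shift by the same amount apart from sampling error between families, and it treats families as the replicates for the effect of TIPS.

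TIPS is delivered and adapted by site, and the protocol predicts that sites will respond differently. The waves are also 3 + 15 = 18 months apart, at calendar dates that differ by region, so local events can move a whole site's scores. Each of these creates variation in change between sites. That variation averages out over 20 sites, not over 2000 families. Leaving it out understates the standard error and favours false-positive findings on all five scales. Recruiting more families per site makes the relative understatement worse.

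**Working it through.** **Inputs from the protocol article.** 20 sites; 300 therapists; 300 × 20 × 0.33 = 1980, stated as 2000 families per wave, so about 2000/20 = 100 per site per wave.

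**Assumed inputs.** Outcome SD 1; site ICC 0.02-0.05; CAC 0.8-0.9 (the correlation between a site's true mean before and after). No ICC, CAC or design effect is given in the document, so a wider range is shown below.

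**The plan's own figure.** Number of Families claims more than 90% power for 0.1 < d < 0.3. With independent families, power at d = 0.1 (two-sided 5%) is 99.98% for 6000 per wave (20 assessed for each of 300 therapists) and 88.5% for 2000 per wave. The claim therefore reproduces only at the larger count and with families taken as independent. The two counts need reconciling, but that is a separate matter; 2000 is used from here on.

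**Variance of the before-after difference.** Let the site-by-period variance be Vsp = ICC × (1 − CAC).

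- Nested intercepts only: Var = 2(1 − ICC)/2000
- With site-by-period variation: Var = 2(1 − ICC)/2000 + 2·Vsp/20
- Actual rejection rate of a nominal 5% test: 2[1 − Φ(1.96 × SE model / SE true)]

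| | ICC 0.02, CAC 0.9 | ICC 0.05, CAC 0.8 |
|---|---|---|
| Vsp | 0.002 | 0.010 |
| Model variance | 0.00098 | 0.00095 |
| Added variance | 2 × 0.002/20 = 0.00020 | 2 × 0.010/20 = 0.00100 |
| Model SE | 0.0313 | 0.0308 |
| True SE | 0.0344 | 0.0442 |
| Ratio | 1.10 | 1.43 |
| Rejection rate | 7.4% | 17.1% |

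**Wider range.** A second version, which also takes out a therapist ICC of 0.05, gives these ratios at 2000 per wave:

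- 1.03 (coverage 94.4%) at ICC 0.01, CAC 0.95
- 1.25 (coverage 88%) at ICC 0.05, CAC 0.90
- 1.82 (coverage 71.8%) at ICC 0.10, CAC 0.80
- exactly 1.00 at CAC = 1

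A simulation of 20 sites × 15 therapists × 7 families per period (4000 runs) agrees: the nested-model 95% interval covers 87.9% at Vsp = 0.005 and 82.2% at Vsp = 0.01.

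**Shared therapists.** Families were allowed to belong to two therapists in the same site. Coverage was 95.3% when half did, 94.5% when all did, and 95.6% when all did with a therapist ICC of 0.15. There is no narrowing.

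**The case against.** The best defence is that the article is condensed. It names grouping levels and does not say that only intercepts are fitted, so a random period slope may sit in an analysis plan that is not shown. This stands to the extent that one can say only that no such term is named. But the article does more than stay silent. It fixes a structure and states its purpose, and an analyst who follows it as written fits a model at odds with the protocol's own hypothesis.

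The second defence is that the size rests wholly on assumed ICC and CAC values. That also stands. The understatement runs from trivial to large, so the conclusion must be conditional. The rejection rates are for a plain 5% test, whereas Šidák-corrected intervals are planned. That correction deals with the number of comparisons and does not repair a standard error that is too small.

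The third defence is that this is a hybrid type 3 study focused on implementation, so the MPOC-20 is not its main outcome. This limits the importance but does not remove the point.

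A reader might infer more than the document supports:

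- **That shared therapists also narrow the intervals.** The simulation shows they do not, because stable therapist effects largely cancel.
- **That families are counted twice within a wave.** Nothing describes this; seeing at least one therapist is an eligibility threshold, and each sample is surveyed once.
- **That "1-time data collection will be undertaken with 2 samples" contradicts "the possibility that families have responded once or twice to the MPOC-20".** Two one-time samples can overlap, and the model allows for that.
- **That the error should be sized at 6000 families per wave.** That count conflicts with the 2000 in Participants and would exaggerate the effect.

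**Conclusion.** The point holds in conditional form and should be acted on. As written, the MPOC-20 model has no term for sites changing by different amounts, so its standard error reflects about 2000 families per wave and not 20 sites. If change varies by site, the before-after intervals for all five scales are too narrow. Under the assumed ICC of 0.02-0.05 and CAC of 0.8-0.9, the true standard error is about 1.10-1.43 times the model's and a nominal 5% test rejects about 7-17% of the time. If site means are almost perfectly stable between waves, nothing material is lost. It cannot be said outright that the intervals are too narrow, because the document does not quantify variation in change between sites.

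The nesting of each family in one therapist is a separate and lesser mis-specification. It does not match eligibility through one or more therapists, and it has no shown effect on interval width.

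**What to change.** 1. State a random site-by-period effect (a random period slope by site) alongside the site, therapist and family intercepts, with small-sample degrees of freedom based on 20 sites. A therapist-by-period effect may be considered, but with about 20 × 0.33 = 6.6 responding families per therapist per wave it may be weakly estimable, so it need not be in the main model.
2. State how families with several participating therapists enter the model: assign one index therapist per family, or cross-classify therapists.

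**Cost.** Both are changes of specification; the index therapist also needs one recorded field. Intervals become wider. With 19 degrees of freedom the critical value is 2.093 instead of 1.960, so at the 5% level the width grows by 1.10 × 2.093/1.960 = 1.17 to 1.43 × 2.093/1.960 = 1.53 over the assumed range. At 2000 families per wave, with the therapist ICC of 0.05 also assumed, power for d = 0.2 stays at 99% or more, while power for d = 0.1 is 81% (ICC 0.02, CAC 0.9) to 59% (ICC 0.05, CAC 0.8). The power statement under Number of Families should be revisited accordingly.

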### Ethics Approval

The research ethics committees overseeing the 20 participating sites will approve this research project. At the time of manuscript submission, the Research Ethics Board of the *Centre intégré de santé et des services sociaux de l’Estrie—Centre hospitalier universitaire de Sherbrooke* approved this project (ID MP-31-2022-4546) along with the Health Research Ethics Board-Health Panel at the University of Alberta (ID Pro00119976). Ethics approvals have also been submitted to the Hamilton Integrated Research Ethics Board and the Human Ethics Board at the University of British Columbia. Finally, ethics submissions are in preparation for the Interdisciplinary Committee on Ethics in Human Research at the Memorial University of Newfoundland, the Izaak Walton Killam Research Ethics Board, the University of Manitoba Ethics Board, and the University of Saskatchewan Human Ethics Board. Informed consent will be obtained before data collection from the participating managers, therapists, and parents. Participants will be informed that the study data will not constitute an evaluation of their professional performance. Data collection will occur entirely on the web using secure data collection and management solutions.

## Results

Funding was provided by the Canadian Institutes for Health Research on July 22, 2021. All 20 sites were recruited for the funding application. Ethics approval for the first participating site (ID MP-31-2022-4546) was received in February 2022 and for the second site (ID Pro00119976) in July 2022; submissions are either in preparation or pending in the other jurisdictions. To prepare sites, manager meetings were conducted between October 2021 and November 2021 to review responsibilities (eg, identification of site leadership members) and discuss timing for study initiation. As a result, data collection is anticipated to start in September 2022 and conclude by September 2024. Data analysis will occur concurrently with data collection until late 2024. Study- and site-specific results will be available for dissemination from early- to mid-2025, with publications available throughout the same year.

## Discussion

### Overview

Telehealth is a feasible, acceptable, and cost-effective service delivery option for pediatric rehabilitation for children experiencing, or at risk for, disability, and has established effectiveness in improving service access, child outcomes, and family satisfaction with pediatric rehabilitation [12,15,16,19,28,29]. However, before the pandemic, adoption in pediatric rehabilitation was low [12,35]. Despite the recent rapid uptake and dramatic increase in the use of telehealth owing to the public health restrictions imposed by the pandemic, many pediatric therapists provided telehealth without appropriate training and support [12].

To fill this gap, this hybrid implementation-effectiveness study aims to (1) evaluate whether the implementation of TIPS will enhance the adoption of FCT interventions by therapists working in different contexts and the contextual factors that may influence their adoption, (2) assess TIPS effectiveness on wait times and families’ perceptions of service quality, and (3) explore costs from a health care perspective. Therapists’ intention to adopt FCT is expected to increase minimally in the short term (ie, 1 month after the implementation of TIPS), as is their fidelity to FCT practices. Modest increases in adoption and in fidelity in the longer term (ie, >1 month after TIPS), with fluctuating engagement over time dependent on therapist, family, organizational, and system factors are anticipated. For sites with the largest effect change in intention to adopt FCT and fidelity of FCT practices, it is hypothesized that wait times will significantly decrease, whereas families’ perceptions of service quality will significantly improve after TIPS implementation. Finally, families’ cost savings after TIPS are anticipated, with managers reporting no additional cost incurred because of TIPS.

Moreover, we hope that this study will generate the knowledge required on how to support therapists in implementing FCT practices within pediatric rehabilitation services. We will also identify the contextual factors that may influence therapists’ adoption of telehealth and affect telehealth effectiveness at therapist, service, and family levels. As a prospective study, this knowledge will be contextualized to support therapists working in varied settings, building local capacity, and ensuring pediatric therapists have the established skills needed to deliver FCT interventions effectively. Study- and site-specific findings will be disseminated to organizational partners via webinar presentations. All training materials will be made readily available across Canada and internationally to facilitate the development of telehealth knowledge and skills more broadly in the current and upcoming national and international pediatric rehabilitation workforce. Training materials, implementation strategies, and study findings may also assist pediatric rehabilitation organizations and their leaders in generating appropriate policies, ongoing training opportunities, and procedures to ensure sustained delivery of comprehensive, high-quality rehabilitation service models, which include telehealth as an option. Finally, the study findings may also be the catalyst for the development of a set of required competencies for physiotherapists, occupational therapists, and speech-language pathologists who use telehealth to deliver rehabilitation services. To ensure wide dissemination to a variety of interested audiences, the study results will be shared as publications, conference presentations, on social media, and via newsletters.

